## Abstract

**Background:**

Excessive gestational weight gain (EGWG) among women with overweight or obesity is a public health concern, increasing the risk of adverse pregnancy outcomes. Although lifestyle intervention has been proved effective on EGWG control, few successful mobile health-based lifestyle interventions exist in healthcare settings.

**Methods:**

The Healthy Gestational Weight Gain program (HGWG-pro) is a two-centered randomized controlled trial that aims to evaluate the effectiveness of a multi-component intervention on promoting appropriate gestational weight gain, preventing gestational diabetes mellitus (GDM), and improving pregnancy, delivery, and neonatal outcomes among overweight or obese pregnant women aged 18 to 40 years old in China. Two maternal and child health care hospitals will be selected from the eastern region of China. Altogether 200 women with pre-pregnancy body mass index (BMI) ranging from 24 to 40 kg/m^2^ from the two hospitals will be randomized to intervention or control group. The intervention will be delivered from 10^+ 0^-13^+ 6^ weeks’ gestation to 32^+ 0^–35^+ 6^ weeks of gestation, with biweekly counseling sessions conducted either face-to-face during routine prenatal visits or via telephone, depending on the participant’s schedule. A smartphone application and wearable smart wristband will be used to assist in providing GWG related information, monitoring dietary behaviors, physical activity and weight, and providing feedback on weight and behaviors for participants. Data will be collected at 8^+ 0^-13^+ 6^, 24^+ 0^-27^+ 6^, and 32^+ 0^-35^+ 6^ weeks’ gestation, at delivery, at 42 days, 6 months and 12 months after delivery. This study has two primary outcomes: the between-group differences in gestational weight gain at 24^+ 0^-27^+ 6^ weeks’ gestation and 32^+ 0^-35^+ 6^ weeks’ gestation. The secondary outcomes will include differences between groups in weekly rate of GWG and incidence of adverse pregnancy complications and pregnancy outcomes, changes in diet, physical activity and other offspring health indicators at follow-up visits. Metabolic blood test results including indicators such as blood sugar and blood lipids will be extracted from the electronic medical record (EMR) system, indicators such as insulin and glycated hemoglobin will be measured through the collected blood samples. This trial includes a variety of process evaluation methods to evaluate the fidelity and adherence of the intervention.

**Discussion:**

The HGWG-pro is one of the few mobile health-based interventions targeting EGWG among women with overweight or obesity in China. This multi-component intervention study is unique in its assessment of long-term maternal and infant health outcomes, extending up to 12 months postpartum, and the intervention methods based on mobile health contribute to yield an intervention model suitable for widespread application in healthcare settings.

**Trial registration:**

ClinicalTrials.gov (NCT06370533): registered on 31th March 2024.

## Background

Excessive gestational weight gain (EGWG) has been a public health concern, with nearly half of pregnant women gaining more gestational weight gain than the Institute of Medicine (IOM) guideline [1]. Women with overweight or obesity before pregnancy are more easily suffering from EGWG than normal-weight women [1–3]. Overweight or obesity before pregnancy itself can increase the risk of pregnancy and delivery complications as well as future obesity, diabetes, and cardiovascular risk [4, 5], while EGWG can further amplify this adverse effect [6, 7]. Thus, it’s of great significance to conduct intervention studies among women with pre-pregnancy overweight or obesity.

Lifestyle intervention is a cost-effective strategy that has demonstrated significant effect on improving gestational weight gain (GWG) [8–10]. Evidences indicated that intensive behavioral lifestyle interventions with in-person counselling were effective in preventing EGWG among overweight or obese women [11, 12]. The Gestational Weight Gain and Optimal Wellness (GLOW) trial introduced telephone-based lifestyle intervention to make the intensive behavioral lifestyle interventions become feasible in healthcare settings and achieved success [13]. However, except that physical activity was evaluated by accelerometer objectively in the GLOW study, other self-monitoring (like weight and diet) and dietary goal setting were performed by traditional ways without the assistance of mobile health.

The emergence of mobile health opens the way for innovative behavioral change intervention approaches. However, a few lifestyle interventions based on mobile health existed and not all of them were effective on GWG control among women with overweight or obesity [14]. Due to the various intervention design across studies, the optimal intervention approach based on mobile health technology (including intervention components, delivery modes and behavioral strategies) is still unknown [15]. Still, many of their dietary intervention targeting low glycemic index (GI) or energy control, which are complex for both women and health care providers [16–18]. In addition, evidence regarding the long-term effects of intervention on maternal and infant health beyond the pregnancy and immediate postpartum period are needed [19]. Thus, based on the components of an efficient GLOW trial and usual antenatal care process in China, we developed the mobile health-based lifestyle intervention, Healthy Gestational Weight Gain program (HGWG-pro). The study was designed to be feasible in healthcare settings with the aim of evaluating the effectiveness of a multicomponent lifestyle intervention compared with the usual antenatal care in preventing EGWG among women with overweight or obesity.

## Methods

### Study design

The HGWG-pro study is a two-center randomized controlled trial. To examine the universality of the intervention in cities with different socio-economic levels in the eastern area of China with a high prevalence of obesity [20], we will select two hospitals from different regions of China: Beijing, whose per-capita GDP is the highest among the 10 eastern provinces, and Shandong, whose per-capita GDP ranks eighth among the ten eastern provinces [21]. Tongzhou Maternal and Child Health hospital and Weifang Maternal and Child Health Hospital will be selected in this program. The process of routine prenatal care in the two hospitals is similar, except that Tongzhou Maternal and Child Health hospital operates a nutrition clinic where all pregnant women are suggested to visit. They are provided with a 20-minute health education session focusing on the essentials of a healthy pregnancy. Furthermore, early-stage pregnant women with a body mass index (BMI) of 28 kg/m² or higher are offered an additional personalized nutrition consultation to support their health during pregnancy. However, this process does not affect our recruitment of participants because all those pregnant women who received the nutrition consultation will be randomly assigned to the intervention or the control group, and the nutrition clinic consultation belongs to the usual care of the hospital, which might not influence the intervention.

The intervention will last for approximately 6 months from 10^+ 0^−13^+ 6^ to 32^+ 0^−35^+ 6^ weeks’ gestation, and it will be implemented from April 2024 to February 2025, according to the time of last enrollment of women in the intervention group. The study will continue to delivery, 42 days, 6 months and 12 months after delivery with collection of delivery information and anthropometric measures. Figure 1 is the flow chart of the study.

**Fig. 1 Fig1:**
[figure not shown]
Flow chart of the HGWG-pro study

### Eligibility and recruitment

The HGWG-pro study will recruit 200 overweight or obese pregnant women from 2 hospitals, with 100 participants from each hospital. Overweight or obesity were determined based on BMI recommendations of the Group of China Obesity Task Force of the Chinese Ministry of Health (overweight: 24 ≤ BMI < 28 kg/m^2^; obese: BMI ≥ 28 kg/m^2^) [22]. Pregnant women receiving usual antenatal care at the two hospitals will be firstly identified through gestational weeks. Only those at 8–14 weeks’ gestation will be further evaluated according to the inclusion criteria: aged between 18 and 40 years, pre-pregnancy BMI between 24 and 40 kg/m^2^ based on weight self-reported and recorded in the electronic medical record (EMR), singleton pregnancy, skilled at using smartphones and WeChat (mobile application), planning to attend regular antenatal care and delivery at Weifang Maternal and Child Health Hospital of Shandong or Tongzhou Maternal and Child Health hospital of Beijing, no contraindications to physical activity according to Physical Activity Readiness Questionnaire (PAR-Q), willing to be randomized and cooperate with regular follow-up visits and sign informed consent.

Exclusion Criteria including women with pre-pregnancy hypertension, severe cardiovascular or cerebrovascular diseases, respiratory disease, hepatic or renal disease, malignant tumors, systemic lupus erythematosus, thyroid disease, severe anemia, and other chronic diseases, cervical insufficiency, multiple pregnancy, continuous vaginal bleeding, diabetes before pregnancy, special dietary needs (e.g. vegetarianism), severe psychiatric disorders, with a history of bariatric surgery or other surgical history involving important organs within 3 months; participated in other clinical trials within 6 months.

### Sample size estimation

The sample size was estimated to ensure adequate power for detecting group differences in GWG at both mid- (24^+ 0^−27^+ 6^ weeks) and late-pregnancy (32^+ 0^−35^+ 6^ weeks). The anticipated differences between the two groups were 2.19 kg [13] at 32^+ 0^−35^+ 6^ gestational weeks, and 1.19 kg at 24^+ 0^−27^+ 6^ gestational week [23], the SD of the gestational weight gain would be 4 kg and 2 kg at both mid- and late-pregnancy, respectively. The rate of attrition would be 10% in each group. We aimed to recruit a total of 200 pregnant women from 2 hospitals, with 100 women per hospital. The sample size will provide 80% power with α = 0.05 to detect a mean difference of 2.19 kg in the gestational weight gain between groups after the intervention from 10^+ 0^ to 13^+ 6^ gestational weeks to 34^+ 0^~35^+ 6^ gestational weeks.

### Randomization

The study will obtain informed consent at the baseline clinic visit at 8^+ 0^ to 13^+ 6^ weeks’ gestation. Only those women who meet the inclusion criteria, consent and complete the baseline assessment will be randomly assigned to either intervention or control group.

The 100 participants from each hospital will be randomly allocated at a 1:1 ratio to either the intervention group or the control group by the study staff, stratified by the categorical variables of age (< 30 and ≥ 30 years), pre-pregnancy BMI (< 28 and ≥ 28 kg/m^2^), and history of delivery with randomly determined block sizes of 4. Neither the staff nor the participants will be blinded to the group assignment due to the nature of the intervention program. The process of the randomization will be supervised by another study staff and recorded in a Microsoft EXCEL database.

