### Fidelity/quality control of the intervention

Data collection and intervention are performed by two key members of the research team, who know the research protocol well. Two operation manuals according to each hospital’s routine perinatal care process have been developed for implementing and managing the intervention. The manuals describe in detail when, where and what the project staff should do in delivering the intervention. Both of the two project staffs will be required to perform the intervention according to the operation manuals.

During the implementation of this intervention, regular online meetings will be held to report the implementation process and record problems and good experiences will also be shared to facilitate the intervention in the future.

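### The Randomization section calls the block size random but names only 4; if it is always 4, up to about 30% of allocations can be known in advance to unblinded staff who track them.

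*Protocol article*

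**What the plan says.** All of the following is from the protocol article.

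- **Allocation** (Randomization): "The 100 participants from each hospital will be randomly allocated at a 1:1 ratio". Members of the study staff make the assignment. The strata are age (two levels), pre-pregnancy BMI (two levels) "and history of delivery with randomly determined block sizes of 4".
- **Timing** (Randomization): a woman is randomised only after she has been found eligible, has consented and has completed the baseline assessment.
- **Blinding** (Randomization): "Neither the staff nor the participants will be blinded to the group assignment due to the nature of the intervention program".
- **Oversight** (Randomization): the process is "supervised by another study staff and recorded in a Microsoft EXCEL database".
- **Roles:** Fidelity/quality control of the intervention states that "Data collection and intervention are performed by two key members of the research team". The section on compliance and retention gives recruitment, survey and intervention to the project staff in the obstetric clinic.
- **Adjustment** (Statistical analyses): models adjust for clustering and for baseline values of the outcome. Age, BMI group and delivery history are not listed as covariates.

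**The concern.** The wording can be read in two ways. It may mean randomly permuted blocks that always hold 4 places, which is the likelier reading. Or it may mean sizes that vary, with the list of sizes lost from the sentence. The two designs differ greatly in how far the next allocation can be foreseen.

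Under the first reading, the published protocol gives the one figure needed to work out the end of each block. Unblinded staff know the arms of women already enrolled. The stratum can be known before a woman is approached: hospital, age, BMI and delivery history come from the record or a simple question.

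There is also room to act on such knowledge. Some eligibility items in Eligibility and recruitment need judgement, such as skill with a smartphone and willingness to cooperate with follow-up. The baseline window of 8+0 to 13+6 weeks allows a woman to be deferred. Staff could, even without meaning to, enrol motivated women when the intervention arm is due. Motivation plausibly affects gestational weight gain, the primary outcome, so the arms could differ for reasons other than the intervention.

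**Working it through.** The plan states no figure for predictability, so there is none to reproduce.

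**Inputs**
- Ratio 1:1; 100 women in each of 2 hospitals; block size 4 (Randomization).
- Strata: 2 hospitals × 2 age groups × 2 BMI groups × 2 levels of delivery history = 16, or 200/16 = 12.5 women each on average. Two levels for delivery history is an assumption, because the article does not give the levels.
- Staff are assumed to know the size and to follow past allocations within each stratum.

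**Complete blocks of 4.** There are 6 equally likely orders of two places per arm. An allocation is certain once one arm has used both its places.

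| Position in block | Certain in advance | Best guess correct |
|---|---|---|
| 1 | 0 | 1/2 |
| 2 | 0 | 2/3 |
| 3 | 1/3 | 2/3 |
| 4 | 1 | 1 |
| Mean | (4/3)/4 = 33.3% | (17/6)/4 = 70.8% |

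The best guess is the arm with more places left.

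**Incomplete last blocks.** A stratum that stops early loses some of the certain positions. With 12 women, 3 × 4/3 = 4 are certain, and 4/12 = 33.3%. With 13, it is 4/13 = 30.8%. With 6, it is (4/3)/6 = 22.2%.

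**Whole trial, by simulation** (1,000 replicates, 200 women):
- 16 equal strata: 30.1% certain, 95% simulation range 27% to 33.5%. That is 0.301 × 200 ≈ 60 women (54 to 67).
- Unequal stratum shares: 29.9% to 30.1%.
- Stratified by hospital only: 33.3%.
- Best guess correct with 16 strata: about 69%.

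**If sizes vary and are hidden from staff** (illustrative sets; the article gives none):
- Sizes 4 and 6: about 6% certain.
- Sizes 2, 4 and 6: about 3% certain.

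**What varied sizes do not change.** Guessing the arm with fewer women so far in the stratum needs no knowledge of the size. Over complete blocks it is right (1/2 + 1)/2 = 75% of the time for size 2, 70.8% for size 4 and 68.3% for size 6. With the three sizes equally likely, the average per allocation is (2 × 0.75 + 4 × 0.708 + 6 × 0.683)/12 ≈ 70%. So varied sizes remove most of the certainty but hardly lower the success of a guess. That depends on who can see the running order.

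**The case against.** Several points on the other side are sound.

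- **The size may vary.** The sentence may be garbled. In that case the 30% does not apply, and 3% to 6% is nearer for the sets tried. This stands, and it makes the figure conditional. The sentence still needs correcting, because it is wrong under either reading.
- **Access is not described.** A reader might infer that recruiters hold the Excel record, or that all past allocations are visible to everyone. The article says neither. It says that staff are unblinded and that another staff member supervises. Nor does it say that the same person recruits and allocates. Who generates and conceals the list is detail that an article commonly leaves to the full protocol, so that silence is not counted here.
- **Assignment already follows consent and baseline.** This rules out early release of the assignment as the problem. What remains is prediction, which can come before a woman is approached.
- **The figure is a ceiling.** It needs staff to know the size, follow 8 strata in each hospital and act on what they find. Nothing shows that they would, and no bias in kilograms has been estimated.
- **Analysis may help.** A reader might infer that such bias could never be removed. That is too absolute: self-efficacy, stage of change, and attitude and knowledge are measured before randomisation (Table 3), so steering could be examined and partly adjusted for. Motivation that these scales miss would remain.

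**Conclusion.** The contradiction in the Randomization section is certain. That the block size is always 4 is the likeliest reading, not an established fact. On that reading, up to about 30% of allocations (about 60 of 200) could be known before enrolment, and the best guess would be right about 69% of the time. Both figures rest on 16 strata and on staff who know the size and follow each stratum. They measure the opportunity for selective enrolment in an open-label trial whose project staff recruit, survey and intervene; they are not evidence that it happened. Adjustment for baseline measures could correct such selection only in part. The point should be corrected, and the change is cheap, but it does not by itself invalidate the trial.

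**What to change.** 1. **Design.** Replace the phrase with block sizes that truly vary at random, for example 2, 4 and 6, and do not disclose them to recruiting staff. State in the methods that sizes vary, and report the actual values after enrolment closes.
2. **Custody.** Have the supervising staff member already planned keep the sequence, and state that this person does not recruit. This matters as much as the sizes, because the running order within a stratum supports a good guess whatever the sizes are.
3. **If enrolment has started or ended.** Baseline assessment was planned for April to August 2024 (Data collection). Apply items 1 and 2 to any women still to be enrolled. Correct the phrase to the sizes actually used. Compare stage of change and self-efficacy at baseline between arms.
4. **Analysis.** Add age, BMI group, delivery history and hospital as covariates in the models under Statistical analyses.

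**Cost.** A new list for the women not yet enrolled, and a few sentences of text. Blocks of 6 allow slightly larger imbalance in small strata. The adjustment now listed does not cover this, which is why item 4 belongs with the change.

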### Control group

Pregnant women randomized to the control group in the two hospitals will not receive any of the HGWG-pro intervention components and will continue their routine antenatal care according to the local hospital’s health care provision.

### Intervention

#### Intervention components

We used the transtheoretical model and stages of change (TTM) to guide the intervention strategies in this multi-component lifestyle intervention program. The intervention will be delivered by two trained members of the project through 12 individual biweekly counseling sessions, including 6 face-to-face sessions and 6 telephone sessions, which were tailored to align with key events in routine prenatal care.

The initial 40-minute face-to-face session (10^+ 0^ to 13^+ 6^ weeks) will cover the following topics: definition of EGWG and its adverse effects on maternal and child health, the recommended gestational weight gain based on Chinese references (Table 1) [24], dietary recommendations from the Dietary Guidelines for Chinese Residents [25],“two not, six less” (healthy eating principles: not eating excessively, not drinking sugar-sweetened beverages, eating less fried food, eating less unhealthy snacks, eating less Western-fast food, eating less takeout, eating less high-sugar desserts, and eating less processed meat), weekly physical activity and weight management goals for pregnancy. The biweekly sessions will be performed through telephone or face to face to provide feedback on behavioral changes and weight gain over the past two weeks based on data from the App and wristband, to review behavioral and gestational weight gain goals, and for participants with poor weight control, a detailed discussion of diet and exercise habits to identify key challenges will be provided, followed by tailored guidance.

**Table 1 Tab1:** Recommended gestational weight gain standards for Chinese pregnant women

Pre-pregnancy BMI Category	Total Gestational Weight Gain	1 st Trimester Weight Gain	2nd & 3rd Trimester Weekly Gain
Underweight (BMI < 18.5 kg/m^2^)	11.0 ~ 16.0 kg	0 ~ 2.0 kg	0.46 kg (0.37 ~ 0.56)
Normal weight (18.5 ≤ BMI < 24.0 kg/m^2^)	8.0 ~ 14.0 kg	0 ~ 2.0 kg	0.37 kg (0.26 ~ 0.48)
Overweight (24.0 ≤ BMI < 28.0 kg/m^2^)	7.0 ~ 11.0 kg	0 ~ 2.0 kg	0.30 kg (0.22 ~ 0.37)
Obese (BMI ≥ 28.0 kg/m^2^)	5.0 ~ 9.0 kg	0 ~ 2.0 kg	0.22 kg (0.15 ~ 0.30)

The intervention will be assisted by mobile health apps and wearable devices. The pregnant women in the intervention group will be equipped with a weight management platform account, a smart wristband (Huawei Wristband 8), a weighing scale, and an Elastic band. Participants will receive in-person training on how to utilize the weight management App of the WeChat Public Account “Population health service platform” and the Wristband. These tools will enable them to access health education resources, track weight gain, monitor dietary behaviors and physical activity, and review feedback about their weight and lifestyle behaviors. Details about the intervention are described in Table 2.

**Table 2 Tab2:** Key intervention components based the smartphone app with the help of wristband

Intervention components	Content
Health education activities	48 articles about weight management during pregnancy are presented in the health education module of the Wechat app, participants are required to read 2 to 4 articles per week from 10^+ 0^ to 35^+ 6^ gestational weeks.
Dietary behavior modification	(1) Dietary goal setting: 8 core dietary goal will be set by the program member according to women’s change intention. The eight eating behavioral goals will be assigned to each participant with two for every 4-week cycle. (2) Dietary behavior monitoring: women will be asked to record the 8 dietary behaviors in the App every week.
Active physical activity	(1) Goal reminding: 150 min MVPA per week, recommending 30 min of aerobic exercise (including brisk walking) 3 times a week and 30 min of resistance exercise 2 times a week; goal of 6000 steps/day) will be shown at the face of the physical activity module. (2) Exercise video providing: a 5 min of Warm-up exercises video, a 30 min of aerobic exercise video and a 30 min of resistance exercise video are provided for women to use. (3) Exercise monitoring: on the one hand, women will be asked to record the physical activity behaviors manually in the app every day, with the function of recording multiple times a day; on the other hand, women’s physical activity will be monitored by wearing a wristband every day, with the function of monitoring heart rate, steps, total physical activity time and different levels of physical activity time. (4) Safety reminding: Articles about how to exercise safety and how to deal with the muscle soreness caused by exercise are provided.
Weight management	(1) Weight gain goal reminding: weight gain goal per week/during the whole pregnancy and current total weight gain will be displayed at the top of the weight record page. (2) Weight monitoring: participants will be asked to record their weight at least one time per week, with the weighing condition of fasting in the morning, emptying urine and feces, and wearing light clothes. All participants in the intervention group will be provided with a weighing scale. (3) Feedback about weight gain: as soon as participants input the current weight, the platform will immediately pop up feedback about weight gain by comparing with last week’s weight.
Feedback	Tailored feedback in the form of graphical illustration and text according to diet, physical activity, and weight data collected by WeChat public account and a wristband. In the assessment feedback interface, participants’ weekly feedback report will be displayed from the following aspects: (1) Weight gain: Your pre-pregnancy weight was XX kg, your initial weight was XX kg, and your weight last week was XX kg. You measured your weight a total of XX times in this week, and your most recent weight is XX kg. Feedback for Good Weight Control (Positive Encouragement): Your weight control during this period has been excellent. Great job! Keep it up! Continue to maintain healthy eating and exercise habits, as your efforts are already showing results. The future looks bright! Feedback for Excessive Weight Gain During Pregnancy (Improvement Suggestions): It appears that your weight gain during pregnancy has been excessive. I suggest focusing on improving your diet and exercise behaviors in the coming weeks. Please weigh yourself weekly and keep a record, and maintain healthy lifestyle habits to ensure a healthy weight gain. Feedback for Rapid Weight Gain During Pregnancy (Improvement Suggestions): Your rate of weight gain during pregnancy has been relatively fast. I recommend paying more attention to your diet and exercise habits. Please weigh yourself weekly and keep a record, and continue to maintain healthy lifestyle habits to regulate the rate of weight gain. (2) Dietary behavior: Feedback based on the pregnant woman’s performance this week and comparison with last week: This week’s performance is good, and it’s as good as last week’s performance. Keep up the great work!/This week’s performance is good, and compared to last week, there has been improvement. Keep up the effort!/This week’s performance is poor, but compared to last week, there has been improvement. Keep pushing!/This week’s performance is poor, and there has been no improvement compared to last week. Put in more effort!/This week’s performance is poor, and there has been a setback compared to last week. You must put in more effort! (3) Physical activity behavior from the record: This week, you recorded exercising XX times, with a total of XX minutes of activity. You have met/failed to meet the goal of 150 min of weekly activity (based on the recorded activity time compared to the target of 150 min). Please keep up the good work. For the health of both you and your baby, make sure to walk more and move more. Don’t forget to record your activity after each exercise session!” (4) Physical activity data from the wristband: This week, your average daily activity distance was XX meters, with XX minutes spent walking, XX minutes spent running, and XX minutes spent on moderate to high-intensity activities. The average calories you burned each day was XX kcal. Your average daily step count was XX steps, and walking at least 6,000 steps per day is beneficial to your health. You achieved the goal on XX days this week (days with ≥ 6000 steps). Maintaining good exercise habits helps keep your body in a healthy state, so please keep up the great work! (5) Heart rate from the wristband: Based on the heart rate data from the wristband, provide feedback on the pregnant woman’s average heart rate and the duration of time spent within the target heart rate. It is recommended that the pregnant woman increase moderate exercise. (6) Sleep quality: Based on the sleep data from the wristband, provide feedback on the sleep situation and recommend 7–9 h of sleep duration (7) Intervention compliance scores: This week, you earned XX points, bringing your total to XX points. Following the intervention plan set by the project team and maintaining a good lifestyle will lead to more health benefits. Keep it up!”
Record reminder	women in the intervention group will receive a reminder to fill in the dietary behavior per week, physical activity behavior per day and weight monitoring results per week.

*MVPA* moderate-to vigorous-intensity physical activity, which was defined as exercise during which the heart rate of participant reaches reaches 40%-60% of the maximum heart rate (220- age[year])

All women who agreed to participate in this study will be enrolled in the online system associated with our WeChat public account. They will be assigned a unique ID. All those services are designed and implemented to ensure the confidentiality of participants ‘information, and data will be used only by project members who have signed a confidentiality agreement.

